### Outcomes (CASE-Cancer, PAM, SUS/EUQ)

The outcomes of this clinical study will be measured and evaluated using CASE-Cancer, PAM, SUS and EUQ. First questionnaire battery (T1) will include CASE-Cancer and PAM, and will be administered in all four batteries (T1–T4) to establish the patients’ baselines. All successive batteries (T2, T3, and T4) will include two additional questionnaires.

The four questionnaire batteries (pre-screening, T1, T2, T3) measure primary outcomes. In the pre-screening questionnaire, additional questions aimed at collecting data on background variables (e.g., demographic data) are foreseen. The questionnaire battery administered at T1, T2, and T3, will also include the patent activation measure. Additional background variables, such as overall satisfaction with the intervention and satisfaction with the system will be assessed at T2 and T3 (directly after the intervention, e.g.,).

### Statistical analysis

Despite this is mainly a pilot study of acceptability, usability and analysis of surrogate variables, sample size is estimated according to expected effectiveness in changing healthy habits in patients. This is based on previous peer-review published studies with mobile devices in cancer survivors.

An article by Pope et al. [75] investigated the impact and feasibility of commercial mobile health applications and social media to improve physical activity and health of breast cancer survivors. They provided a digital health education intervention to breast cancer survivors. The results show positive post intervention trends in increased average daily moderate-to-vigorous physical activity and steps. The results of the study show a notable decrease in weight (2.4 kg) and body fat percentage (2.3%). Quintiliani et al. [76] aimed to evaluate engagement (use and acceptability), physiological (weight), behavioral (diet and physical activity), and other secondary outcomes among Breast Cancer Survivors. The engagement was high: the mean number of days recording steps via the wristband pedometer, recording a weight via scale, and responding to text messages was high, and 100% of participants completed all 4 calls with the counselor. The mean weight of participants decreased. The daily intake of fruit and vegetables increased, and self-reported moderate physical activity, measured in metabolic equivalent of task (MET) minutes per week, increased [76]. Most of the participants would very likely participate again and would recommend the app to others.

#### Sample size calculation

To estimate the sample size to difference between two dependent means we have based on the assumptions of a two-sided confidence level of 95%, a statistical power of 90% and effect size Cohen’s *d* of 0.25. The previous assumptions indicate that 160 patients may detect differences between pre and post variables of healthy habits. A G*Power 3.1 software was used to make this sample size estimation.

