#### Primary and secondary endpoints

The primary endpoint is defined as: *increased perceived self-efficacy in participants (80 colorectal, 80 breast cancer survivors from the 4 pilot hospitals) following the mHealthApp supported intervention as measured using CASE-cancer scale for cancer as the validated standardized measure.*

The secondary endpoints include:observing modifications in patient activation levels measured using the PAM,observing modification in User acceptance depending on the level of support measured via SUS and UEQ,description of negative outcomes over time: hospitalization, exacerbations, treatment adherence, depression, recurrence, drug escalation,impact of variable modes of delivery (e.g., conversational agent) on quality of answers measure with DQS,the impact of patient trajectories (extracted from retrospective data) and PGHD on prediction of possible secondary disease or negative outcome,the impact of patient trajectories (extracted from retrospective data) and PGDH on improved intervention against the appearance of secondary diseases, worsening late toxicities or development of fatal events (sudden death, suicide).

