#### Study setting

The study will involve 160 survivors (80 survivors of Breast Cancer and 80 survivors of Colorectal Cancer) from four countries, Belgium, Latvia, Slovenia, and Spain. Each of the sites will recruit 40 cancer survivors according to the inclusion/exclusion criteria. Study will involve the use of digital intervention during every-day activities outside the clinical environment (i.e., at the subjects’ homes). The data collected will be evaluated during regular 6 month follow ups.

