#### Statistical analysis

A descriptive analysis of clinical characteristics will be performed. The quantitative parameters will be summarized by its average ± standard deviation and percentiles, while for the qualitative variables the frequencies and percentages will be computed correspondingly.

In order to test the objectives, for CASE-cancer, SUS/UEQ and scores as well as for single items, differences between pre, post, and follow-up measurements will be analyzed by parametric test (Student’s *t*-test/ANOVA), non-parametric test (Wilcoxon signed-rank test) and McNemar test (for categorical measures).

Descriptive statistics of the negative outcomes and/or complications (hospitalization, exacerbations, treatment adherence, depression, reoccurrence and drug escalation) reported in the study will be used. These measures and patient trajectories (appearance of secondary diseases, worsening late toxicities or development of fatal events) will compare with data extracted from retrospective study. We will use univariate tests like Student’s *t*-test and chi-square test and multivariate models. For all the comparisons, sub-analyses will be carried out stratifying by type of cancer, sex and any other variable considered of interest.

An intention-to-treat analysis and sensitivity analysis of observed data will be performed. We will use R 3.4.2 and SPSS version 19 for statistical analysis. Test results with a *p* value below 0.05 will be deemed statistically significant.

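### The stated inputs give 171 complete pairs, not 160; 160 is also the recruited total, and the calculation is not tied to CASE-cancer, the primary endpoint

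*Protocol article*

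**What the plan says.** The Sample size calculation section of the protocol article describes a calculation for the difference between two dependent means. Its inputs are "a two-sided confidence level of 95%, a statistical power of 90"%, and "effect size Cohen’s *d* of 0.25", run in G*Power 3.1. The conclusion drawn is: "The previous assumptions indicate that 160 patients may detect differences between pre and post variables of healthy habits".

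The same figure is the recruitment target. Under Study setting, "Each of the sites will recruit 40 cancer survivors according to the inclusion/exclusion criteria", and there are four sites, so 4 × 40 = 160. The section on patient information and informed consent repeats 160 as the total to be recruited. Measurements follow at six-month steps from T1 to T4.

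The primary endpoint, under Primary and secondary endpoints, is "increased perceived self-efficacy in participants (80 colorectal, 80 breast cancer survivors from the 4 pilot hospitals"), measured on the CASE-cancer scale. The Hypothesis section likewise predicts a significant increase in self-efficacy. Healthy habits are not in the list of primary and secondary endpoints, although the Study itinerary section says that they will also be analysed. The analysis section sets the decision rule: "Test results with a *p* value below 0.05 will be deemed statistically significant".

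**The concern.** The article gives every input needed to recompute the sample size, and the result should match. If it does not, the 90% power is misstated before any patient is lost. Because the calculated number and the recruited number are the same, the stated power also presumes that everyone recruited supplies both measurements.

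The calculation is attached to healthy habits, while the hypothesis and the primary endpoint concern self-efficacy on CASE-cancer. A reader who meets a non-significant CASE-cancer result would naturally judge it against 90% power for d = 0.25. The stated inputs do not give that power, and the article never linked it to that endpoint.

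**Working it through.** **Inputs, all from Sample size calculation.** Paired design, one group; two-sided α = 0.05, which agrees with the 0.05 threshold in Statistical analysis; power 0.90; d = 0.25. I read d as the mean change divided by the SD of the change, the natural reading for a test of two dependent means in the named software.

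**Attempt to reproduce 160, normal approximation.**

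n = (z₀.₉₇₅ + z₀.₉₀)² / d² = (1.960 + 1.2816)² / 0.0625 = 168.1, so 169.

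**Exact paired t-test.** Power is the probability that a noncentral t variable with n − 1 degrees of freedom and noncentrality d√n falls outside ±t₀.₉₇₅,ₙ₋₁.

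- n = 170: power 0.8999
- n = 171: power 0.9016

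The required number is therefore 171 complete pairs. The stated 160 is 11 short.

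**Could a variant explain 160?**

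- One-sided 5% with 90% power: 139.
- Two-sided with 80% power: 128. Inflating for 20% loss gives 128 / 0.80 = 160, but that is 80% power, and no such allowance is stated.
- Two-sided with 88% power: 160.
- Two-sided, 90% power, d = 0.26: 158. With d = 0.255: 164.
- Wilcoxon signed-rank with efficiency 3/π: 179.

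No variant that keeps the stated inputs gives 160.

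**What 160 does give.** Because 160 is also the recruited total, the number of complete T1–T4 pairs is 160 × (1 − loss). The article states no loss rate, so the 10% and 20% rows are assumptions that show the range.

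| Assumed loss by T4 | Complete pairs | d√n | Power at d = 0.25 | d detectable with 90% power |
|---|---|---|---|---|
| 0% | 160 | 3.162 | 88.2% | 0.258 |
| 10% | 144 | 3.000 | 84.6% | 0.272 |
| 20% | 128 | 2.828 | 80.2% | 0.289 |

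**Sizing variable against primary endpoint.** The opening of Statistical analysis and the Sample size calculation both size the study on healthy habits. The two studies described there as the basis report weight, body fat, steps, physical activity, diet and engagement; no self-efficacy result is given for either. The endpoint section names CASE-cancer. Nothing in the article links d = 0.25 to that scale.

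**The case against.** The strongest reply is that the numerical error is minor. With complete data the gap is 90.0 − 88.2 = 1.8 percentage points, the detectable effect moves from 0.250 to 0.258, and no design decision turns on it. That stands. It limits the severity but does not make the stated number correct.

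A second reply is that this is mainly a pilot, openly sized on a surrogate. The disclosure is genuine. Yet the article still presents a formal power calculation, predicts a significant increase in self-efficacy and sets a significance threshold, so the power it quotes should be right and should be related to the primary endpoint.

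A third reply is that a dropout allowance or a missing-data method may sit in a fuller document. An intention-to-treat analysis is planned, CASE-cancer is measured at four time points, and a condensed article need not describe how missing data are handled. This also stands in part. A reader might infer that the trial will have only about 80% power. The article does not support that, because it gives no loss rate. What it does show is that the calculated and recruited numbers are identical, so no inflation is visible.

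A reader might also infer that healthy habits are not an outcome of the study at all. That goes too far: the Study itinerary section says they will be analysed, and the Abstract expects them to improve. The accurate statement is that they are absent from the list of primary and secondary endpoints.

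**Conclusion.** The point holds and should be fixed. The stated inputs require 171 complete pairs (169 by the normal approximation), and 160 complete pairs give 88.2% power. This rests on d being in units of the SD of change and on a two-sided 5% paired t-test.

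The arithmetic error alone is small. Two further facts add to its weight. The same 160 is the recruited total, so any loss by T4 takes power further below 90%; the amounts shown for 10% and 20% are illustrations. And the power statement concerns healthy habits, so none is given for CASE-cancer.

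A reader might conclude that the trial is too small and needs more patients. The documents do not support that: 160 remains a workable number if the claim made for it is restated.

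**What to change.** Keep 160 and replace the 90% claim with wording such as:

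> 160 participants with T1 and T4 data give 88% power (paired t-test, two-sided 5%) for a standardised mean change of 0.25 SD of change; 90% power holds for 0.258. With an assumed 10% / 20% missing T4, power is 85% / 80% and the effect detectable with 90% power is 0.272 / 0.289.

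State this for the T1–T4 change in CASE-cancer, as a detectable effect, in place of healthy habits. Moving 0.25 to CASE-cancer without comment would replace one unsupported power statement with another. The text should therefore say that 0.25 was not derived from CASE-cancer data, unless a justification on that scale is supplied.

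The cost is a text change. No extra patients are needed, and the stated power becomes slightly less favourable.

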#### Statistical analysis

A descriptive analysis of clinical characteristics will be performed. The quantitative parameters will be summarized by its average ± standard deviation and percentiles, while for the qualitative variables the frequencies and percentages will be computed correspondingly.

In order to test the objectives, for CASE-cancer, SUS/UEQ and scores as well as for single items, differences between pre, post, and follow-up measurements will be analyzed by parametric test (Student’s *t*-test/ANOVA), non-parametric test (Wilcoxon signed-rank test) and McNemar test (for categorical measures).

Descriptive statistics of the negative outcomes and/or complications (hospitalization, exacerbations, treatment adherence, depression, reoccurrence and drug escalation) reported in the study will be used. These measures and patient trajectories (appearance of secondary diseases, worsening late toxicities or development of fatal events) will compare with data extracted from retrospective study. We will use univariate tests like Student’s *t*-test and chi-square test and multivariate models. For all the comparisons, sub-analyses will be carried out stratifying by type of cancer, sex and any other variable considered of interest.

An intention-to-treat analysis and sensitivity analysis of observed data will be performed. We will use R 3.4.2 and SPSS version 19 for statistical analysis. Test results with a *p* value below 0.05 will be deemed statistically significant.

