## Methods/design

### Study design

A single-case experimental prospective study was designed in alignment with single-case experimental design (SCED) methodology [42]. Within SCED, each individual is his/her own control group based on the first measurement prior to the intervention. The SCED was selected since single-case designs can capitalize on the ability of technology to easily, unobtrusively, and repeatedly assess health-related behavior [43]. The study design is highlighted in Fig. 1. It is based on the Changing Criterion design in which the intervention and delivery of intervention are modified through personalization of (a) goals/tasks and (b) with spoken language interfaces and embodied conversational agents to complement the regular baseline delivery mode via the digital interfaces of the mHealthApp. The study will take place between 1st of May 2021 and 31st of December 2022, with the recruitment period between 1st of April 2021 and 15th May 2021. Data collection is first carried out prior to intervention, during recruitment round (T1). Each recruited individual will sign a letter of consent and fill in CASE-cancer and PAM questionnaires. The SUS questionnaire responses, along with CASE-Cancer and PAM will be collected following a baseline phase (T2) which will last for 6 months. During this phase a ‘generic’ intervention will include a recording of the diary (at least 3 times a week), report regarding their emotional state (at least once a day) and answering a specific PRO for reporting Health Related QoL and symptoms (a different PRO each day). In total, we expect 10–15 min of interaction every day. T2 will conclude with the first follow-up with clinician, during which data regarding primary (CASE-Cancer, PAM, SUS/EUQ) and secondary endpoints will be collected. The personalized intervention phase (T3) will include execution of tasks on mHealth App personalized for the survivor. The data collection tools will remain the same, however the responsible oncologist will define which of the tools the patient must implement (e.g., which PROs) and in what frequency, depending on the risk assessment implemented by the clinical staff. During intervention, specific tools may change depending on the risks detected for the specific patient. T3 concludes with a follow-up during which data regarding primary/secondary endpoints (CASE-Cancer, PAM, SUS/UEQ). A first comparison between generic intervention and personalized intervention will be made. The AI supported clinical intervention (T4) will introduce embodied conversational agent EVA [44] and AI-drive risk assessment engine to deliver fully personalized intervention and to demonstrate that the data-driven models developed within PERSIST can improve quality of life of cancer survivors by acquiring, managing, sharing, and processing big data to create overall actionable insights at the point of care.

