#### Patient information and informed consent

Clinical partners will develop an informed consent document translated in their local language and will apply for their local or national bioethics committee approval. GDPR regulation will be strictly followed to protect personal data of participants. Each center will be responsible to obtain a signed informed consent from the patient before inclusion in the study. The participants will be recruited by 4 hospitals involved in the study from different EU countries (Belgium, Latvia, Slovenia and Spain). Every clinical partner will involve 40 survivors, 20 patients from C18/C19 (Colorectal cancer) and 20 patients from C50 (breast cancer). In total 160 patients will be recruited to participate in envisioned two-phases clinical study. The recruitment stage will begin in April, 2021. The study will involve breast and colorectal cancer patients who have survived beyond curative cancer treatment. We will consider a survivor patient all breast and colorectal cancer patients who survive without recurrence beyond 3–24 months after the end of treatment (surgery ± radiation therapy ± chemotherapy), they have received. For colorectal cancer survivors' group, two subgroups will be included (chemotherapy and non-chemotherapy). None of the groups will be lower than 33% in ratio to the other. For breast cancer survivorspatients that have had surgery and patients that have had chemotherapy.

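### The pre-post change is tested as one unadjusted sample, although recruitment is fixed in eight hospital-by-cancer cells and no committed analysis shows the change by hospital

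*Protocol article*

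**What the plan says.** The section on patient information and informed consent fixes the recruitment structure: "Every clinical partner will involve 40 survivors, 20 patients from C18/C19 (Colorectal cancer) and 20 patients from C50 (breast cancer"). With four hospitals in four countries this gives eight cells of 20.

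The sample size section works with a single paired sample. It begins "To estimate the sample size to difference between two dependent means", assumes "a two-sided confidence level of 95%, a statistical power of 90% and effect size" d = 0.25, and concludes that "160 patients may detect differences between pre and post variables of healthy habits". It mentions no hospital or cell.

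Under Statistical analysis, for CASE-cancer, SUS/UEQ and other scores, "differences between pre, post, and follow-up measurements will be analyzed by parametric test" (t-test or ANOVA), by the Wilcoxon signed-rank test or by McNemar's test. No model terms are given. The multivariate models appear only in the paragraph on negative outcomes and the retrospective comparison. For all comparisons, "sub-analyses will be carried out stratifying by type of cancer, sex and any other variable considered of interest". Cancer type and sex are named; hospital and country are not.

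Two places bear on delivery. The section on training sessions offers demonstration workshops at some of the hospitals only. The study design section says that in the personalised phase "the responsible oncologist will define which of the tools the patient must implement", guided by a risk assessment of the individual patient.

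On the target of inference, the hypothesis speaks of participants, and the primary endpoint is tied to the survivors from the four pilot hospitals. The abstract's discussion states the expected result for cancer survivors without that limit.

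**The concern.** The design balances recruitment on two factors, hospital and cancer type, but the named primary tests use neither. Two consequences follow.

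First, when sampling is in fixed cells of equal size, differences in mean change between cells are not sampling error of the overall mean. An unadjusted paired test counts them as noise, so precision that the design has already provided is discarded.

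Second, there is no control arm, so the mean within-person change is the whole of the evidence for the hypothesis. A paired test removes stable differences in level between hospitals, but not differences in how much patients change. Training differs between hospitals by plan, so unequal change is plausible. If the change occurred in one hospital only, the pooled test could still be significant and the result could be read as a general effect in four countries.

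**Working it through.** **Inputs.** From the article: n = 160, d = 0.25, two-sided 5% level, target power 90%, four hospitals of 40, eight cells of 20. Assumed, because the article gives no figure: the share R² of the variance of change explained by the eight cells, taken as 5% or 10%.

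**1. The plan's own figure.** For a paired t-test the noncentrality is d√n = 0.25 × √160 = 3.16 on 159 df. Two-sided power is 88.2%, within two points of the stated 90% (exactly 90% would need 171 complete pairs, which is a separate matter). The 88.2% is the reference value below.

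**2. Cost of ignoring the cells, with the four hospitals as the target.** If the cells explain R², the residual SD is √(1 − R²) times the total SD. The pooled standard error is therefore too wide by the factor 1/√(1 − R²), and the standardised effect becomes d/√(1 − R²) on 160 − 8 = 152 df.

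| R² (assumed) | pooled SE / stratified SE | effective d | power with cells |
|---|---|---|---|
| 0 | 1.000 | 0.250 | 88.1% |
| 5% | 1.026 | 0.256 | 89.7% |
| 10% | 1.054 | 0.264 | 91.2% |

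The first row shows that 7 degrees of freedom cost almost nothing if the cells explain nothing. The error rate points the same way: with hospital effects on the change of ±0.10, ±0.25 or ±0.50 SD that cancel overall, the pooled test's simulated two-sided error is 4.9%, 4.4% or 2.9%, at or below the nominal 5%.

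**3. Can one hospital carry the result?** The pooled test is significant once the mean change reaches t(159; 0.975)/√160 = 1.975/12.65 = 0.156 SD. With no change in three hospitals of equal size, the fourth needs 4 × 0.156 = 0.62 SD (in units of the total SD of change). If that hospital changes by 1.0 SD, the pooled mean is 1.0/4 = 0.25, exactly the planned effect, and with a within-hospital SD of 1 the pooled test is significant in about 84% of simulated trials.

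**4. Would a check by hospital reveal it?** For a heterogeneity test of the change on 3 and 156 df, the noncentrality is 40 × Σ(hospital mean − overall mean)² = 40 × 0.75 × D² when one hospital changes by D and the rest by zero (within-hospital SD 1).

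- D = 1.0: noncentrality 30.0, power 99.8%.
- D = 0.62: noncentrality 11.5, power 81%.

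**5. Precision of each hospital's estimate.** The 95% half-width at n = 40 is t(39; 0.975)/√40 = 2.023/6.325 = 0.32 SD. Power to detect d = 0.25 within one hospital is about 34%, so these estimates are for judging consistency, not for four separate claims.

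**The case against.** The strongest objection is that centre terms and tables by centre usually belong in a statistical analysis plan, which is not shown, and that ANOVA could include such terms. The article also allows sub-analyses by any further variable of interest, and cancer type, one half of the cell structure, is already named. Much of this stands: hospital is not excluded, and the study describes itself as mainly a pilot. But the article is not simply silent. It names the tests for the primary comparison and names strata, and the list leaves out the factor on which recruitment was fixed. An open-ended allowance commits nobody to looking at hospital.

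A second objection also stands. Fixed cells alone do not cure the one-hospital problem. With changes of 1.0, 0, 0 and 0 SD the cell-adjusted test has the same mean and a smaller standard error, and is significant in about 88% of trials against about 84% for the pooled test. Only the hospital-specific estimates and the heterogeneity test address that concern.

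Third, local delivery should not be overstated. The oncologist's choice of tools follows the individual patient's risk. The workshops are the only stated difference between hospitals, and training materials and technical support are offered without such a limit. A change confined to one hospital is an illustration, not a prediction, and equal quotas cap each hospital at a quarter of the sample.

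A reader might infer more: that the pooled error bars are wrong, or that clustering within hospitals makes the standard error too small and inflates the error rate. The documents do not support this. It would require treating the four hospitals as a random sample of a wider population, whereas the hypothesis and primary endpoint are framed on participants from the pilot hospitals. It would also require a between-hospital variance of change, which the article does not give.

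**Conclusion.** The concern holds in a limited form. For the endpoint as defined, the pooled test is valid and slightly conservative. Under an assumed R² of 5% to 10%, the standard error is about 3% to 5% too wide and power is 88.2% where 89.7% to 91.2% is available; if the cells explain nothing, nothing is lost. These figures assume 160 complete pairs.

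The more useful half concerns interpretation. About 0.62 SD in one hospital with none in the other three reaches significance, and no committed analysis would show that pattern, although a simple heterogeneity test would usually detect it at this sample size. The abstract's broader wording makes this matter more, because it invites a conclusion that goes beyond the endpoint's own limits. This is a worthwhile and nearly free improvement, not a flaw that invalidates the primary test.

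**What to change.** In the Statistical analysis section:

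- Analyse the change in CASE-cancer, and the other repeated scores, with a repeated-measures model that includes the eight hospital-by-cancer cells as fixed effects. Keep hospital fixed, because four hospitals are too few for reliable random-effect inference.
- Beside the pooled result, report the four hospital-specific changes with 95% confidence intervals and a hospital-by-visit test.
- Name hospital among the planned strata, next to cancer type and sex.
- Word the conclusion for the four pilot hospitals throughout, as the primary endpoint does and the abstract's discussion does not.

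Cost: a change of wording and up to 7 degrees of freedom. No new data are needed, since hospital and cancer type are known from recruitment. The conclusion becomes slightly narrower.

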
**Fig. 1 Fig1:**
[figure not shown]
The design of the single-case experimental prospective study

During the final follow-up, the data regarding the primary/secondary endpoints will be collected. To measure the overall impact of the digital intervention we will adapt the Model for the Assessment of Telemedicine (MAST) methodology [45]. The patient domain will be assessed through CASE-cancer, PAM, SUS, UEQ. The clinical relevance will be assessed by: (i) analyzing the impact of Big Data prediction models to support decision-making in patient follow-up, and (ii) the impact of the intervention on against the appearance of secondary diseases, worsening late toxicities or development of fatal events (sudden death, suicide).

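### The univariate tests named for the comparison with retrospective data ignore time at risk, and no common follow-up window is set, so unequal follow-up alone can give a significant difference in either direction

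*Protocol article*

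**What the plan says.** The final Statistical analysis subsection of the protocol article first plans descriptive statistics for the negative outcomes: "hospitalization, exacerbations, treatment adherence, depression, reoccurrence and drug escalation". It then says that these measures and the patient trajectories ("appearance of secondary diseases, worsening late toxicities or development of fatal events") "will compare with data extracted from retrospective study". The tools come in the next sentence, which opens "We will use univariate tests like", names Student's t-test, and ends "chi-square test and multivariate models". A p value below 0.05 counts as significant. An intention-to-treat analysis and a sensitivity analysis of observed data are announced for the study as a whole.

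Under Primary and secondary endpoints, the corresponding item is a "description of negative outcomes over time". Under Study design, the paragraph after Fig. 1 lists "the impact of the intervention on against the appearance of secondary diseases" as one of two ways in which clinical relevance will be assessed; late toxicities and fatal events are in the same item.

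Prospective follow-up consists of T2, T3 and T4 at 6-month steps after T1, within a study running from 1 May 2021 to 31 December 2022. The article gives no size or follow-up length for the retrospective data.

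**The concern.** Most of the listed outcomes are events, and the chance of having had at least one rises with the time observed. A chi-square test compares the proportions with an event, and a t-test compares means per patient. Neither uses the length of observation. If one group is watched for longer, it shows more events even when the rate is identical.

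This is separate from who enters each group. With the same eligibility and the same hazard the tests still show a difference, so matching on eligibility alone would not remove it.

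At stake is how the clinical-relevance result is read. The prospective study has no concurrent control, and the retrospective data are the only external comparator named for these events. A p value below 0.05 could be taken as an effect of the intervention when it reflects only the calendar.

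**Working it through.** The article gives no figure for this comparison, so there is none to reproduce.

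**Inputs from the article.** Prospective n = 160. Follow-up is 3 × 6 = 18 months (1.5 years). The significance level is 0.05, taken as two-sided, so 2.5% per side.

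**Assumptions, because the article gives no values.** The same constant hazard h in both groups (no effect of the app): 5% per year, with 3% and 8% as a range. 500 retrospective patients, with 160 as an alternative. Retrospective windows of 12 to 60 months.

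**Step 1: proportion with an event.** p(t) = 1 − exp(−h·t). At h = 0.05, the prospective proportion is 1 − exp(−0.075) = 7.2%.

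**Step 2: chi-square without continuity correction**, as z = (p̂₁ − p̂₂) / √[p̄(1 − p̄)(1/160 + 1/500)]. The probabilities that z falls below −1.96 (false benefit) or above 1.96 (false harm) are summed over the two binomial distributions.

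| Retrospective window | Retrospective proportion | Apparent risk ratio | False benefit | False harm |
|---|---|---|---|---|
| 12 months | 4.9% | 1.48 | 0.1% | 22% |
| 18 months | 7.2% | 1.00 | 2.0% | 2.9% |
| 24 months | 9.5% | 0.76 | 12% | 0.2% |
| 36 months | 13.9% | 0.52 | 64% | 0% |
| 60 months | 22.1% | 0.33 | over 99% | 0% |

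Hand check at 36 months: the difference is 0.0723 − 0.1393 = −0.0670. The pooled proportion is (160 × 0.0723 + 500 × 0.1393)/660 = 0.123, the standard error is 0.0298, and the expected z is −2.25, already past −1.96. At 12 months: the difference is +0.0235, the standard error 0.0206, and the expected z +1.14.

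**Step 3: sensitivity to the assumptions.**
- Hazard 3% per year: false benefit of 8%, 41% and 96% at 24, 36 and 60 months, and about 17% false harm at 12 months.
- Hazard 8% per year: false benefit of 18%, 84% and 100%, and about 30% false harm at 12 months.
- 160 retrospective patients at 5% per year: false benefit of 11%, 51% and 97%, and about 13% false harm at 12 months.

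**Step 4: drop-out alone, equal planned windows.** Let 20% leave evenly over 18 months, with later events unseen and the denominator kept at 160. A leaver's average proportion is 1 − (1 − e^−0.075)/0.075 = 3.7%. The prospective proportion is 0.8 × 7.2% + 0.2 × 3.7% = 6.5%, a risk ratio of 0.90. False benefit rises from 2.0% to about 4%.

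**Step 5: does time at risk cure it?** A Wald test of the log rate ratio per person-year was simulated with no effect at 10% yearly risk, with retrospective windows of 1, 1.5, 3 and 5 years, drop-out up to 30%, and 160 or 1,000 retrospective patients. It gave 1.8% to 2.7% false benefit and 1.6% to 3.3% false harm, near the nominal 2.5% per side.

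**The case against.** The strongest objection is that a journal article gives this comparison two sentences, and that the retrospective window, index date and censoring rule belong in a full protocol or analysis plan that is not shown. That is fair for those details alone. It does not cover the named tests. Student's t-test and chi-square are a stated choice, and they do not suit accruing events unless follow-up is equal and complete.

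Several stronger readings are tempting, and the article does not support them:

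- **That every analysis ignores time.** The word that makes the list of univariate tests open, and the undefined multivariate models, leave room for a method that uses follow-up. The defect is certain only for the tests named. An undefined model does not repair them, since their p values would still be read at 0.05.
- **That the app will look protective.** The retrospective follow-up is unknown. A shorter window makes the app look harmful.
- **That events are analysed as bare counts, or that a participant who leaves is scored event-free.** Neither is written. The first is an inference from the tests, and the article gives no rule for events in lost participants.
- **That the endpoints section treats the retrospective data as a control arm.** It does not: it calls the negative outcomes a description and uses retrospective data as the source of trajectories. The comparison appears under Statistical analysis, and the reading as impact of the intervention under Study design.
- **That drop-out is as serious as unequal windows.** Its effect is modest by comparison.

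It is also true that equal windows alone bring chi-square back to about 2% false benefit if follow-up is complete, so the common window does most of the work. Finally, treatment adherence and depression need not be accruing events, and the named tests may serve them.

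**Conclusion.** The point stands in a limited form. For outcomes that accrue with time, the univariate tests named do not use time at risk, and the text does not align the two follow-up windows. A significant difference in either direction can then arise with no true effect. Its size depends on assumed hazards, retrospective sample size and windows: at 5% per year and 160 against 500, it runs from about 22% false harm with a 12-month window to about 64% false benefit with a 36-month window. The actual direction and size cannot be known from the article. The change should be made, but the comparison is secondary, the article describes the study as mainly a pilot, and the CASE-cancer primary endpoint is untouched.

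**What to change.** In the Statistical analysis section:

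1. Cut retrospective follow-up at the same 18 months, counted from an index date at a comparable time since the end of treatment.
2. Compare accruing events per person-time (a rate model with a person-time offset, suited to hospitalization and drug escalation) or by a time-to-event method (suited to recurrence, secondary disease and death). Censor at last contact, and treat death as a competing event where relevant.
3. Keep these models simple. At 5% per year, 160 × 0.072 is only about 12 prospective events.
4. Keep the t-test and chi-square for measures that do not accrue, such as treatment adherence or depression scores.

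The cost is a few sentences of analysis text, an index date for each retrospective patient, and last-contact dates for censoring. The downside is that retrospective events after 18 months go unused, so intervals are wider.
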